**6.3 Report of serious adverse events**

Serious adverse events (SAEs) meeting the definition, including laboratory abnormalities meeting the definition of serious adverse events, occurring within 30 days from the signing of the informed consent form to the completion of the last medication, must be reported to the designated person in the study document immediately (within 24 hours after the researchers know). The serious adverse event report form must also be completed and sent to the person specified in the study document within 24 hours of the investigator's knowledge.

Each serious adverse event should be followed up until it is resolved or stabilized, and an updated report should be submitted to the designated person. A single grade 4 laboratory abnormality (according to CTCAE version 4.0) is not reported as a serious adverse reaction unless the investigator considers that the abnormality has met the criteria of the international coordination meeting for serious adverse events (see definition in section 6.3.2). The level 4 laboratory examination abnormalities of CTCAE version 4.0 as the manifestation of the disease in the baseline period should not be reported as serious adverse events, especially when these abnormalities are still allowed or not excluded by the protocol. If there is doubt as to whether the abnormality should be reported as a serious adverse event, the researcher may consult the research supervisor. The abnormal laboratory examination of CTCAE level 4 should be recorded in the "laboratory data" page and checked regularly by the medical inspector.

According to local laws and regulations, serious adverse events must be reported to the ethics committee and FDA.

**7 Appendix**

**7.1 ECOG**

| **Score** | **Description** |
| --- | --- |
| 0 | Fully active, able to carry on all pre-disease performance without restriction (Karnofsky 90-100) |
| 1 | Restricted in physically strenuous activity but ambulatory and able to carry out work of a light or sedentary nature, e.g., light house work, office work (Karnofsky 70-80) |
| 2 | Ambulatory and capable of all selfcare but unable to carry out any work activities. Up and about more than 50% of waking hours (Karnofsky 50-60) |
| 3 | Capable of only limited selfcare, confined to bed or chair more than 50% of waking hours (Karnofsky 30-40) |
| 4 | Completely disabled. Cannot carry on any selfcare. Totally confined to bed or chair (Karnofsky 10-20) |

**7.2 TNM stage**

The tumor stage of each patient was determined based on the AJCC-TNM system.

1. Definitions for T, N, M

***Primary Tumor（T）***

- - - TX：Primary tumor cannot be assessed
    - T0：No evidence of primary tumor
    - Tis：carcinoma in situ: intramucosal carcinoma (involvement of lamina propria with no extension through muscularis mucosae)
    - T1：Tumor invades the submucosa (through the muscularis mucosa but not into the muscularis propria)
    - T2：Tumor invades the muscularis propria
    - T3：Tumor invades through the muscularis propria into the pericolorectal tissues
    - T4：Tumor invades the visceral peritoneum or invades or adheres to adjacent organ or structure
    - T4a：Tumor invades through the visceral peritoneum (including gross perforation of the bowel through tumor and continuous invasion of tumor through areas of inflammation to the surface of the visceral peritoneum)
    - T4b：Tumor directly invades or is adheres to adjacent organs or structures.

***Regional Lymph Nodes（N）***

- - - NX：Regional lymph nodes cannot be assessed
    - N0：No regional lymph node metastasis
    - N1：one to three regional lymph node are positive
    - N1a：one regional lymph node is positive
    - N1b：two or three regional lymph nodes are positive
    - N1c：No regional lymph node are positive, but there are tumor deposits in the subserosa, mesentery, or nonperitonealized pericolic or perirectal/mesorectal tissues
    - N2：Four or more regional lymph nodes are postive
    - N2a：Four to six regional lymph nodes are positive
    - N2b：Seven or more regional lymph nodes are positive

***Distant Metastasis（M）***

- - - MX：Distant metastasis cannot be assessed
    - M0：No distant metastasis by imaging, etc.; no evidence of tumor in distant sites or organs
    - M1：metastasis to one or more distant sites or organs or peritoneal metastasis is identified.
    - M1a：Metastasis to one site or organ is identified without peritoneal metastasis
    - M1b：Metastasis to two or more sites or organs is identified without peritoneal metastasis
    - M1c：Metastasis to the peritoneal surface is identified alone or with other site or organ metastases

**Anatomic stage/prognostic Groups**

***Stage 0*** Tis, N0, M0

***Stage IA*** T1, N0, M0

***Stage IB*** T2, N0, M0

***Stage IIA*** T3, N0, M0

***Stage IIB*** T4a, N0, M0

***Stage IIC*** T4b, N0, M0

***Stage IIIA*** T1-2, N1/N1c, M0

T1, N2a, M0

***Stage IIIB*** T3-4a, N1, M0

T2-3, N2a, M0

T1-2, N2b, M0

***Stage IIIC*** T4a, N2a, M0

T3-4a, N2b, M0

T4b, N1-2, M0

***Stage IVA*** any T, any N, M1a

***Stage IVB*** any T, any N, M1b

**7.3 RECIST criteria**

**Measurable Lesion：**Tumour lesions: Must be accurately measured in at least one dimension (longest diameter in the plane of measurement is to be recorded) with a minimum size of:

• 10 mm by CT scan (CT scan slice thickness no greater than 5 mm; see Appendix II on imaging guidance).

• 10 mm caliper measurement by clinical exam (lesions which cannot be accurately measured with calipers should be recorded as non-measurable).

• 20 mm by chest X-ray.

Malignant lymph nodes: To be considered pathologically enlarged and measurable, a lymph node must be 15 mm in short axis when assessed by CT scan (CT scan slice thickness recommended to be no greater than 5 mm).

**Non-measurable Lesion：**All other lesions, including small lesions (longest diameter <10 mm or pathological lymph nodes with 10 to <15 mm short axis) as well as truly non-measurable lesions. Lesions considered truly non-measurable include: leptomeningeal disease, ascites, pleural or pericardial effusion, inflammatory breast disease, lymphangitic involvement of skin or lung, abdominal masses/abdominal organomegaly identified by physical exam that is not measurable by reproducible imaging techniques.

**Target Lesion：**At most 2 lesions can be selected as target lesions in all measurable lesions of each organ, and at most 5 representative lesions can be selected as target lesions in all involved organs. All target lesions should be recorded and measured at baseline. These five lesions should be selected according to their size (the longest diameter of the lesion) and the repeatability of accurate measurement (whether imaging technology or clinical measurement). The sum of the longest diameter (LD) of all target lesions will be taken as the total LD at baseline. The total LD in the baseline period will be used as the reference value to objectively evaluate the tumor response by measuring the size of future lesions. If there are more than 5 measurable lesions, those not selected as target lesions will be regarded as non target lesions together with unmeasurable lesions

**Non-target lesion：**It includes all unmeasurable lesions (or sites) and all measurable lesions except the five selected target lesions. These lesions need not be measured, but should be recorded as "present" or "not present" at baseline and at each follow-up.

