**5.1.3.1 Primary Study Endpoint**

Primary endpoint：Objective Response Rate (ORR, complete or partial response according to RECIST version 1.1).

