**Evaluation of response**

Complete Response (CR): Disappearance of all target lesions. Any pathological lymph nodes (whether target or non-target) must have reduction in short axis to <10 mm.

Partial Response (PR): At least a 30% decrease in the sum of diameters of target lesions, taking as reference the baseline sum diameters.

Progressive Disease (PD): At least a 20% increase in the sum of diameters of target lesions, taking as reference the smallest sum on study (this includes the baseline sum if that is the smallest on study). In addition to the relative increase of 20%, the sum must also demonstrate an absolute increase of at least 5 mm. (Note: the appearance of one or more new lesions is also considered progression).

Stable Disease (SD): Neither sufficient shrinkage to qualify for PR nor sufficient increase to qualify for PD, taking as reference the smallest sum diameters while on study.**靶The evaluation of Target lesion and non-target lesion**

| **Target lesion** | **non-target lesion** | **New lesion** | **Response** | **requirements** |
| --- | --- | --- | --- | --- |
| CR | CR | No | CR | confirmed after more than 4 weeks |
| CR | Non-CR/non-PD | No | PR | confirmed after more than 4 weeks |
| PR | Non-PD | No | PR |  |
| SD | Non-PD | No | SD | At least 4 weeks from baseline |
| PD | Any | No or yes | PD | No-SD/PR/CR |
| Any | PD | No or yes | PD |  |
| Any | Any | Yes | PD |  |

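### Appendix 7.3 sums target lymph nodes by longest diameter but judges nodes by short axis elsewhere, so PR, SD and PD can depend on which axis is read

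*Protocol*

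**What the plan says.** All the measuring rules are in Appendix 7.3 of the protocol (RECIST criteria).

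- **Measurability of a node:** "a lymph node must be 15 mm in short axis when assessed by CT scan".
- **Choice of target lesions:** "These five lesions should be selected according to their size (the longest diameter of the lesion", together with repeatability of measurement. Nodes are not treated separately.
- **The reference sum:** "The sum of the longest diameter (LD) of all target lesions will be taken as the total LD at baseline". Its use follows at once: "The total LD in the baseline period will be used as the reference value to objectively evaluate the tumor response".
- **Nodes in CR** (Evaluation of response): "Any pathological lymph nodes (whether target or non-target) must have reduction in short axis to <10 mm". This wording confirms that a node may be a target lesion.
- **PR:** "At least a 30% decrease in the sum of diameters of target lesions, taking as reference the baseline sum diameters".
- **PD:** "At least a 20% increase in the sum of diameters of target lesions, taking as reference the smallest sum on study", with an absolute increase of at least 5 mm.

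The primary endpoint in section 5.1.3.1 is "Objective Response Rate (ORR, complete or partial response according to RECIST version 1.1". Section 3.7.4.2 has tumour measurements entered in the CRF by RECIST 1.1, without naming an axis. Sections 3.7.1 and 5.1.3.2 also define a depth of response, which needs the same measurements.

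**The concern.** One node is handled on two axes within one response assessment. Short axis decides whether it can be measured and whether it has resolved. Longest diameter decides its rank among candidate targets and, on the only definition given, what it adds to the sum. The PR and PD definitions do not name an axis, so they do not settle the matter.

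The stake is the primary endpoint. ORR is a count of CR and PR among 28 patients, and PR turns on whether the sum has fallen by 30%. An assessor who follows the sentence on the baseline total and one who carries the appendix's short-axis treatment of nodes into the sum can read the same scan differently. PD calls use the same sum, so PFS and DCR are exposed as well, and so is depth of response.

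**Working it through.** **Design figure.** Section 3.1 gives a Simon minimax design of 15 + 13 = 28 patients for 15% against 35%, one-sided 5%, power 80%. An exact binomial search reproduces N = 28 with 15 in the first stage (continue with more than 2 responses, positive with more than 7; type I error 0.046, power 0.803). Those cut-offs are not the ones the protocol states, which is a separate matter. Only the denominator of 28 is used here.

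**Inputs.** The thresholds (30% fall for PR; 20% rise and 5 mm for PD) come from Appendix 7.3. The protocol holds no patient measurements, so all lesion sizes below are assumed. Every assumed node has a baseline short axis of at least 15 mm and so is measurable.

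**Formula.** Percent change = (follow-up sum − reference sum) / reference sum. Baseline is the reference for PR; for PD it is the smallest sum on study, taken here to be baseline. Each node enters once by longest diameter and once by short axis. Non-nodal lesions enter by longest diameter both times.

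| Assumed case | Longest diameter throughout | Short axis for the node |
|---|---|---|
| 1. Node 24x16 → 20x11 mm | (20−24)/24 = −16.7%: SD | (11−16)/16 = −31.3%: PR |
| 2. Node 28x18 → 22x9, liver 30 → 22 mm | 58 → 44 = −24.1%: SD | 48 → 31 = −35.4%: PR |
| 3. Node 30x16 → 20x13, liver 20 → 15 mm | 50 → 35 = −30.0%: PR | 36 → 28 = −22.2%: SD |
| 4. Node 28x16 → 30x23, liver 20 → 21 mm | 48 → 51 = +6.3%, +3 mm: not PD | 36 → 44 = +22.2%, +8 mm: PD |

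Cases 1 and 2 gain a response under short axis and case 3 loses one, so the change runs both ways. Case 4 shows a PD call changing.

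**Why the sums differ.** The two axes of a node may change in different proportion. The node's weight in the sum also depends on the axis: in case 2 it is 28/58 = 48.3% of the baseline sum by longest diameter and 18/48 = 37.5% by short axis. With no nodal target the two sums are identical.

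**Where CR is protected.** A lone target node going from 28x18 to 21x9 mm falls only (21−28)/28 = −25% by long axis, short of PR. Its short axis of 9 mm nevertheless meets the nodal CR criterion, which does not use the sum. The effect on ORR is therefore mainly PR against SD in patients without target-lesion CR.

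**Size per patient.** 1/28 = 3.6 percentage points of ORR.

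**The case against.** The strongest reply is that the protocol names RECIST 1.1 throughout: for the endpoint, for the six-weekly assessment and for the CRF entries. On that view the appendix is a loose summary and assessors will apply the full criteria. This lowers the chance of harm but does not remove the fault. Appendix 7.3 is the only place where the protocol spells out how the sum is formed. A general citation beside an explicit sentence on longest diameters leaves two instructions standing. The CRF requirement does not ensure that the short axis is recorded, and a later correction would then mean re-reading scans.

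A second reply is that measurability, CR and the sum are separate rules, and that a longest-diameter sum compared with a longest-diameter baseline is consistent within a patient. That is fair. It rules out one inference a reader might draw, that the short-axis change is the true one and the long-axis reading an error. The protocol names no true axis for the sum. What it shows is an inconsistency with consequences for classification.

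Three further inferences are also unsupported. Nodes are not chosen as targets by short axis: 15 mm decides measurability only, and ranking is by longest diameter. Complete responses are not lost through the sum, because CR has its own nodal test. No net bias in ORR follows, because the assumed cases go in both directions.

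**Conclusion.** The inconsistency is real and sits within Appendix 7.3. For patients with nodal target lesions and no target-lesion CR, the choice of axis can decide PR against SD, in either direction, and can decide PD. Each reclassified patient is worth 3.6 points of ORR.

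The conclusion that classification can change rests on the appendix text and its thresholds; the worked sizes only illustrate it. The protocol does not say how many patients will have nodal targets, nor how their axes will change, so neither the size nor the sign of the net effect on ORR can be given. A reader might infer that the trial's overall decision is likely to be wrong. The documents do not support that. They support only that the written rule leaves the primary endpoint open to two readings.

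**What to change.** In Appendix 7.3, under Target Lesion, replace the sentence defining the baseline total with one that names the axis: *the sum of diameters, taking the longest diameter for non-nodal target lesions and the short axis for nodal target lesions*. Short axis is proposed for nodes because the appendix already uses it for their measurability and for CR. The sponsor should check the sentence against the RECIST 1.1 text that the protocol cites.

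Then:

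- use this one sum at baseline and at every follow-up, for PR, SD, PD and depth of response;
- point the PR, SD and PD definitions under Evaluation of response to it, and align the sentence on choosing targets by size;
- add a CRF field for the axis measured on each target lesion.

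The cost is one sentence with its cross-references and one CRF field. No extra scans are needed. If measurements have already been taken, nodal targets recorded by longest diameter only would have to be re-read on the existing images.

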**Evaluation of response**

Complete Response (CR): Disappearance of all target lesions. Any pathological lymph nodes (whether target or non-target) must have reduction in short axis to <10 mm.

Partial Response (PR): At least a 30% decrease in the sum of diameters of target lesions, taking as reference the baseline sum diameters.

Progressive Disease (PD): At least a 20% increase in the sum of diameters of target lesions, taking as reference the smallest sum on study (this includes the baseline sum if that is the smallest on study). In addition to the relative increase of 20%, the sum must also demonstrate an absolute increase of at least 5 mm. (Note: the appearance of one or more new lesions is also considered progression).

Stable Disease (SD): Neither sufficient shrinkage to qualify for PR nor sufficient increase to qualify for PD, taking as reference the smallest sum diameters while on study.**靶The evaluation of Target lesion and non-target lesion**

| **Target lesion** | **non-target lesion** | **New lesion** | **Response** | **requirements** |
| --- | --- | --- | --- | --- |
| CR | CR | No | CR | confirmed after more than 4 weeks |
| CR | Non-CR/non-PD | No | PR | confirmed after more than 4 weeks |
| PR | Non-PD | No | PR |  |
| SD | Non-PD | No | SD | At least 4 weeks from baseline |
| PD | Any | No or yes | PD | No-SD/PR/CR |
| Any | PD | No or yes | PD |  |
| Any | Any | Yes | PD |  |

**Remission time**

The remission time should be calculated from the time when CR or PR (no matter who was recorded first) was first met, until the date of recurrence or progression of the disease was first recorded.。

**Time of Stable disease**

The stable time of the disease should be calculated from the time of the beginning of treatment until the progression of the disease. The minimum measured value of the lesion from the beginning of treatment was used as the reference.

**7.5 Flow-chart of study**

|  | Before-treatment | 21days for one cycle | | | | At the end of study | At the end of study to PD | After PD_10_ |
| --- | --- | --- | --- | --- | --- | --- | --- | --- |
|  |  | 1^st^ cycle | 2^nd^  cycle | 3^rd^  Cycle | 4^th^  to PD or treatment terminated |  |  |  |
| Items | Screening | Day1 | Day1 | Day1 | Day1 | Within 7 days | Every 8 weeks | Every 3 months |
| Informed consent of patients | X（within 28 days） |  |  |  |  |  |  | The following information was collected by telephone or outpatient visit every 2 months  1. Survival information of patients;  2. Changes in the treatment of cancer, including all new treatments |
| Medical History _1_ | X（within 7 days） |  |  |  |  |  |  |  |
| Complete physical examination_2_ | X（within 7 days） |  |  |  |  |  |  |  |
| Inclusion/exclusion Criteria | X |  |  |  |  |  |  |  |
| Random | X |  |  |  |  |  |  |  |
| Vital signs and ECOG |  | X | X | X | X | X | X |  |
| ECG | X（within 28 days） |  | X | X | X | X |  |  |
| CT and MRI _3_ | X（within 28 days） |  | | | |  |  |  |
| Imaging Evaluation_4_ | X（within 28 days） | X （每6周)-- -------------🡪 | | | | | |  |
| Hematological Examination_5_ | X（within 7 days） |  | X | X | X | X |  |  |
| Biochemical examination_6_ | X（within 7 days） |  | X | X | X | X |  |  |
| Urine test_7_ | X（within 7 days） |  | X | X | X | X |  |  |
| Serum pregnancy test | X（within 7 days） |  | | | | |  |  |
| QLQ_8_ |  | X_9_ |  |  | Before 5^th^ cycle or 9^th^ cycles | X |  |  |
| Use Drug |  | X | X | X | X | X |  |  |
| AE evaluation | -- -------------🡪 | | | | | | |  |
| Concomitant disease and drug combination | -- -------------🡪 | | | | | | |  |

1. Complete medical history, demographic data, previous surgery history, concomitant diseases, allergic history, and smoking history.
2. Complete physical examination, ECOG score, NYHA heart disease classification, height, weight, vital signs and detailed examination of the body system
3. Only patients with neurological symptoms at baseline required head CT / MRI to exclude brain metastases
4. During chemotherapy, tumor assessment is performed every 8 weeks. After treatment, CT scan was required every 8 weeks until the disease progressed. If the patient withdraws from the study due to disease progression, a review of CT scan is not required at the end of the study。
5. Hematological test: hemoglobin, hematocrit, platelet, leukocyte, neutrophil absolute value, lymphocyte absolute value, which can be checked one day before each course of treatment。
6. Biochemical tests: blood glucose, calcium, phosphorus, sodium, potassium, chlorine, creatinine, blood urea nitrogen, total protein, albumin, alanine aminotransferase, aspartate aminotransferase, alkaline phosphatase, total bilirubin, etc., which can be checked one day before each course of treatment.
7. Urine tests: urine specific gravity, PH value, urine sugar, urine protein and occult blood. In the screening period, urine test is required in the laboratory, and urine test paper can be used in the subsequent course of treatment.
8. Patients should be followed up every 3 months until 1 year or death.

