| Duration of study participation | The investigational drug will be repeatedly administered until the criteria for discontinuation are met. In the event that the treatment is discontinued for reasons other than an exacerbation of the underlying disease via imaging (e.g., unacceptable side effects), tumor evaluation follow-up will continue until either an exacerbation of the underlying disease is observed via imaging or a new anticancer treatment is initiated, whichever happens first. |
| Administration method | Eligible patients were given sintilimab intravenously at a dose of 200mg on day 1, and anlotinib orally at a dosage of 12mg daily from days 1-14 every 3 weeks. Treatment was maintained until progressive disease (PD), treatment intolerance, death, or withdrawal of consent, with one cycle as 3 weeks. |
| Safety evaluation | Evaluations will be performed using CTCAE version 5.0. |
| Efficacy evaluation | The efficacy will be evaluated in accordance with RECIST version 1.1 every 6 weeks.  ・Image evaluation: computed tomography (CT) or magnetic resonance imaging (MRI) |
| Observations and tests | Physical examination, vital signs, PS, laboratory tests (hematology and biochemistry), urinalysis, tumor markers, ECG, CT of chest, abdomen, and pelvis, etc. |
| Trial Design | APICAL-CRC trial was an investigator-initiated, open-label, non-randomized, single-arm, phase II clinical trial using Simon’s minimax two-stage design. The combination of anlotinib plus sintilimab is expected to result in an improved ORR of 35%. The null hypothesis, which stated that the true ORR was 15%, would be tested against a one-sided alternative of 35%, with 80% power and a type I error rate of 5%. In the first stage, the study accrued 15 patients. If less than two response or no response was observed, the study was terminated and deemed negative. Otherwise, an additional 13 patients would be accrued for the second stage. The study was considered positive if there were more than 9 responders among the 28 patients. |

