**3.7.1 Efficacy Evaluation**

The antitumor effect will be evaluated in accordance with RECIST version 1.1 every 6 weeks.

The primary study endpoints for the study were objective response rate (ORR, complete or partial response according to RECIST version 1.1).

Secondary study endpoints included disease control rate (DCR, the proportion of patients who achieved a complete response, a partial response, or stable disease), progression-free survival (PFS), overall survival (OS) as well as safety.

PFS was defined as the time from therapy initiation to progression according to RECIST.

OS is defined as the time from therapy initiation to death from any cause.

Depth of response (DPR) was defined the percentage of maximum tumor reduction achieved in treatment compared with baseline. In case of CR, DPR is 100%.

Remission maintenance time was calculated in all PR or CR patients who were confirmed to meet RECIST 1.1 criteria. The duration of remission is the time from the first record to PR or Cr until death or disease progression (based on the first occurrence). As of the date of analysis, the deadline was the date of their last imaging evaluation.

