**3.7.4.2 Imaging Evaluation**

- Screening Phase: CT or MRI scans of the chest and abdomen must be performed within 28 days before enrollment, and the measurement of the tumor should be recorded in CRF according to RECIST 1.1
- Treatment Phase：CT or MRI scan should be performed at least every 6 weeks + / - 5 days to evaluate the lesions, and the measurement of tumor should be recorded in CRF according to RECIST 1.1. Other examinations were performed according to the symptoms.
- At the end of the study：CT or MRI scan was used to evaluate the lesion, and the measurement of tumor was recorded in CRF according to RECIST 1.1. Other examinations were performed according to the symptoms。

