**3.8.2 Treatment Phase**

The treatment period was 21 days. The efficacy was evaluated every 2 courses. The laboratory examination, imaging assessment and AE assessment in the treatment stage are shown in the flow chart.。

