**3.8.3** **At the end of the study**

At the end of study (not due to progression), the patients should be examined every 3 months until the disease progresses (see the flow chart).

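### The tumour assessment interval is 6 weeks in the text but 8 weeks in the flow-chart note on treatment, and 3 months or 8 weeks off treatment, so scan-dated endpoints depend on which passage is followed

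*Protocol*

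**What the plan says.** **On treatment.** The synopsis states "The efficacy will be evaluated in accordance with RECIST version 1.1 every 6 weeks", and 3.7.1 repeats it: "The antitumor effect will be evaluated in accordance with RECIST version 1.1 every 6 weeks". Section 3.7.4.2 adds a window: "CT or MRI scan should be performed at least every 6 weeks + / - 5 days to evaluate the lesions". Section 3.8.2 gives the cycle length ("The treatment period was 21 days") and asks for efficacy evaluation after every two courses. The imaging row of the flow chart in 7.5 also says every 6 weeks, in Chinese. Note 4, which annotates that row, says "During chemotherapy, tumor assessment is performed every 8 weeks. After treatment, CT scan was required every 8 weeks until the disease progressed".

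**Off treatment, not yet progressed.** The synopsis requires tumour evaluation to continue until imaging progression or new anticancer treatment, without giving an interval. Section 3.8.3 says "the patients should be examined every 3 months until the disease progresses (see the flow chart". In the flow chart, both the heading of the column running from end of study to progression and note 4 say every 8 weeks.

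**Coverage.** Section 3.7.4.2 says of screening that "CT or MRI scans of the chest and abdomen must be performed within 28 days before enrollment". The synopsis lists "CT of chest, abdomen, and pelvis, etc" among the observations and tests.

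**Endpoints.** PFS runs from start of therapy to RECIST progression, and remission duration ends at progression or death. Nothing in the protocol says which passage prevails where two disagree.

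**The concern.** A RECIST progression can be recorded only when a scan is done, so the scan interval is part of the definition of PFS and of remission duration. If the interval is ambiguous, the progression date is too. There are two separate conflicts.

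The first is 6 against 8 weeks on treatment, where the flow-chart row and its own footnote disagree. The chart is what staff are likely to book visits from.

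The second is 8 weeks against 3 months once drug is stopped, where 3.8.3 refers the reader to a chart that says something else. This one also raises a question of bias. If scans become sparser when drug stops, patients who stop for toxicity have progression recorded later than patients still on drug. A single-arm trial has no comparator in which such a shift would cancel, and its PFS will be read against other trials with their own schedules.

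**Working it through.** **1. The protocol's own figure.** Two courses of 21 days: 2 × 21 = 42 days = 6 weeks. So 3.8.2 agrees with the synopsis, 3.7.1, 3.7.4.2 and the chart row.

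**2. Can note 4 be fitted in?** The window in 3.7.4.2 is 42 − 5 = 37 to 42 + 5 = 47 days. Eight weeks is 56 days, which is 56 − 47 = 9 days past the upper edge. In cycles it is 56 / 21 = 2.67. Neither the window nor the cycle grid absorbs it.

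**3. Off treatment.** Three months is about 13 weeks, against 8 weeks in the column heading and in note 4. These cannot both be the interval.

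**4. Effect of 6- versus 8-weekly scans on PFS.** The protocol assumes no PFS for this trial. As an illustration I take exponential progression with a true median of 6.3 months, the figure the protocol cites for regorafenib plus nivolumab in previously treated patients, and vary it from 4 to 12 months. One month is 4.348 weeks, so 6.3 months = 27.39 weeks. Progression is dated at the next scheduled scan, at interval d.

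- Observed median = ceil(true median / d) × d
- Mean dating delay = d / (1 − exp(−λd)) − 1/λ, with λ = ln 2 / true median

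At 27.39 weeks, λ = 0.0253 per week and 1/λ = 39.52 weeks:

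- d = 6: ceil(4.57) × 6 = 30 weeks = 6.9 months; delay 42.60 − 39.52 = 3.1 weeks
- d = 8: ceil(3.42) × 8 = 32 weeks = 7.4 months; delay 43.65 − 39.52 = 4.1 weeks

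| True median (months) | Observed, 6-weekly | Observed, 8-weekly | Difference | Mean delays (weeks) |
|---|---|---|---|---|
| 4 | 4.14 | 5.52 | 1.38 | 3.12, 4.21 |
| 5 | 5.52 | 5.52 | 0 | 3.10, 4.17 |
| 6.3 | 6.90 | 7.36 | 0.46 | 3.08, 4.13 |
| 8 | 8.28 | 9.20 | 0.92 | 3.06, 4.11 |
| 10 | 11.04 | 11.04 | 0 | 3.05, 4.08 |
| 12 | 12.42 | 12.88 | 0.46 | 3.04, 4.07 |

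The difference in medians depends on where the true median falls on each scan grid, and it can change sign. At 7 months (30.44 weeks), 6-weekly scans give 36 weeks and 8-weekly scans give 32 weeks, a difference of −0.92 months. In size it stays within 0 to about 1.4 months. The mean delay is the steadier measure: about 1 week longer at 8 weeks throughout. In simulated samples of 28 patients with ±5 days of scan jitter and a true median of 6.3 months, the average observed median was about 7.2 months (6-weekly) and 7.4 months (8-weekly), again about 1 week apart.

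**5. Effect of sparser scans after stopping drug.** With the same 6.3-month model, mean dating delay at a 3-month interval is 6.9 weeks, against 3.1 at 6 weeks and 4.1 at 8 weeks. A patient followed 3-monthly after stopping is therefore dated on average 6.9 − 3.1 = 3.8 weeks later than one scanned 6-weekly. To see the effect on the whole trial, I assumed that 10 to 30% of patients stop at a uniform time within 26 weeks and then move to 3-monthly scans. The observed median stayed at 6.9 months for a true median of 6.3. For true medians of 4 to 12 months the shift ran from 0 to no more than about 1 month.

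**The case against.** The strongest reply is that this is a drafting slip of limited consequence. Four text sections and the chart row agree on 6 weeks on treatment. Note 4 speaks of chemotherapy, which this regimen does not contain, so it may be carried over from another protocol. PFS is a secondary, descriptive Kaplan-Meier estimate with no hypothesis attached, and the two-stage decision rests on best overall response. All of that stands and limits the size of the point. It does not tell the investigator which passage to follow, and it does not touch the off-treatment conflict, which the on-treatment statements cannot settle.

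A reader might infer more than the documents support in five ways:

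- **A PFS shift of 2 months or more.** Scanning everyone 3-monthly from first dose would give an observed median of 9.0 months against 6.9. No passage provides for that; 3.8.3 applies only after treatment ends without progression.
- **Variation between sites.** There is one centre. The issue is which passage its investigator follows.
- **A missing pelvic baseline.** Section 3.7.4.2 makes chest and abdomen mandatory, and the synopsis adds the pelvis. Both can be followed together, so this is a loose statement of coverage, not a contradiction, and it does not show harm to best response.
- **That 6 weeks ± 5 days is stated throughout.** Only 3.7.4.2 gives the window.
- **That 3.8.3 plainly orders 3-monthly scans.** It says patients are examined. Because it runs until progression and cites the chart, it still conflicts with the chart's 8-week column.

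The chart's 6-weekly arrow may also extend into the off-treatment column. The extracted table does not settle this, and nothing here rests on it.

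**Conclusion.** The contradiction is real and should be removed. On treatment it is 6 against 8 weeks, and the stated window does not bridge the gap. Off treatment it is 3 months against 8 weeks, through a cross-reference that leads to the conflicting figure.

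The consequence falls on PFS, remission duration and time of first response. The effect on the primary ORR is small, though the date of the first scan can affect who counts as efficacy-evaluable and how disease control is recorded. The size is modest: about 1 week in mean dating delay between 6- and 8-weekly scans. Any one observed median could move by anything from nothing to about 1.4 months, depending on the scan grid. The off-treatment conflict matters more for the direction of bias than for the overall median, because it ties the recorded date to treatment status.

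These figures rest on exponential progression, one interval used throughout for the 6- versus 8-week comparison, and a median borrowed from another trial and varied from 4 to 12 months. The contradiction itself needs none of these assumptions.

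**What to change.** Reconcile note 4, the flow-chart column from end of study to progression, and 3.8.3 with 3.7.1, 3.7.4.2 and 3.8.2, so that one imaging schedule is stated once and cited elsewhere. The investigator should choose the interval; this review does not. Whatever is chosen should:

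- be counted in calendar time from first dose, with a stated window;
- not change when drug is delayed or stopped;
- continue until progression or new anticancer treatment, as the synopsis already requires.

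In 3.8.3, say whether an examination means imaging. State the required scan coverage once, for baseline and follow-up, in line with the synopsis list.

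If patients have already been scanned under differing readings, report the actual scan dates and intervals alongside PFS, separately for time on and off treatment.

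Cost: alignment of text, and possibly a few scans for patients off treatment without progression. The sample size and the two-stage rule do not depend on the scan interval and need no change on this account.
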